## Methods and analysis

### Study design

The trial is a multicenter, prospective, double-blind crossover randomized controlled trial (RCT). The overall process is in Figure 2. In this study, we will include 62 moderate to severe post-stroke hemiplegia patients who had stable disease after 1 year of conservative treatment in multiple neuro medical centers in the General Hospital of the People’s Liberation Army of China et al. All patients included in the study will undergo deep brain electrode implantation. They will be randomly postoperatively divided into a DBS group and a control group, with 31 patients in each group. 1 month after surgery, the DBS group will be given electrical stimulation treatment, while the control group will undergo routine observation. Following up in the 3rd and 6th months after surgery. After the follow-up, all patients will stop electrical stimulation treatment for 2 weeks. After the 2-week washout period, the control group will start electrical stimulation treatment, and the DBS group will continue observation. Outpatient follow-up in the 6th and 9th months after surgery. After the follow-up, all patients will undergo electrical stimulation treatment. Observe for a long time. The leading outcome measure of follow-up is the pre-and post-change score on the Fugl-Meyer Assessment Upper Extremity Scale (FMA-UE). In addition, we will follow up on changes in the secondary outcomes of balance function, neuropsychiatric behavior, Post-stroke Spasticity, fall risk, activities of daily living, and quality of life.

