### Methods

#### Sample size

This study is a randomized, double-blind, active sham stimulation control design, and statistical experts determined that the sample ratio between the DBS group and the control group was 1:1. A review of the literature revealed that subjects’ upper limb FMA scores improved by an average of 7 points. Since this study was based on the changes in the mean FMA before and after DBS treatment, based on literature data, the mean FMA before DBS treatment was 21.92 ± 6.30, and the mean FMA after DBS treatment was 35.42 ± 12.23. This study is designed as a difference test to determine whether the mean of the DBS group (u1) is different from the mean of the control group (u2) (41, 42). The assumptions are as follows: H0: u1 − u2 = 0, H1: u1 − u2 ≠ 0. The two-sided significance level was 5%, the statistical power was 90%, and the dropout rate was 20% (43). The total sample size required for this study was calculated by PASS V.15 sample size calculation software to be 48 patients, with 24 people in each group. According to the possibility of electrode implantation deviation and other special circumstances leading to a lose, we included 62 patients, 31 in each group.

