### Main outcome

#### Motor function intervention effect

The main evaluation index of this study is the improvement of patients’ motor function before and after deep brain stimulation, which is being evaluated through changes in the Fugl-Meyer Assessment Upper Extremity Scale (FMA-UE) (7). FMA-UE is widely used in clinical motor function assessment and is a quantitative stroke-specific scale used to assess motor function, balance, sensation, and joint function in patients with hemiplegia. Each of the five areas contains different assessment items that are scored on a 3-point scale. This scale has good validity and reliability in the stroke population. The scale covers 50 items, with a total score of 226 points (46). There are 17 sports items, with a total score of 100 points, of which the upper limb motor function score is 66 points, the lower limb motor function score is 34 points. The higher the assessment score, the better the patient’s motor function (47).

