
### Data analysis

All data analysis will based on IBM SPSS Statistics 25.0, describing the total score of each scale at each follow-up and the change from baseline at each visit after treatment. Measurement data using mean ± standard deviation to describe. Count data Use numerical values (%) to describe, and use group t-test or Wilcoxon to compare between groups according to the characteristics of the data. Intra-group comparisons were performed using rank sum-test, paired t-test or paired signed rank-test. For comparisons of pre-and post-treatment change values based on baseline general information, appropriate multivariate analysis models were used to correct for the effects of confounding factors or covariates based on the data situation. The single-item count data of each scale used the chi-square test or the exact probability test, and the grade data used the Wilcoxon rank sum test. A paired rank sum test and repeated measures analysis of variance were used to analyze the changes in score data within the group before and after treatment. The effectiveness measurement index is the improvement rate of each clinical scale at different follow-up times = (scale score at each postoperative time point − preoperative score) / preoperative score * 100%. A score improvement rate > 25% is considered effective. Safety observation indicators are all postoperative adverse reactions, including surgery-related adverse reactions, device-related adverse reactions, and stimulation-related adverse reactions. The type, number of cases, occurrence time, treatment measures, and prognosis of adverse events are recorded. The incidence of adverse events is defined as the number of patients in which it occurs divided by the number of all patients, and an adverse event rate of less than 5% is considered safe.

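### Data analysis makes a percentage improvement rate above 25% the measure of effectiveness, in conflict with the FMA-UE point difference that is primary and that the trial is sized for

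*Protocol article*

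**What the plan says.** All references are to the protocol article.

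- **Primary outcome.** The abstract makes FMA-UE the primary metric. Study design says: "The leading outcome measure of follow-up is the pre-and post-change score on the Fugl-Meyer Assessment Upper Extremity Scale (FMA-UE". Outcome measurements repeats this, and the section on the motor function intervention effect describes motor improvement "which is being evaluated through changes in the Fugl-Meyer Assessment Upper Extremity Scale (FMA-UE").
- **Hypothesis and size.** Sample size asks "whether the mean of the DBS group (u1) is different from the mean of the control group (u2"), with "H0: u1 − u2 = 0, H1: u1 − u2 ≠ 0". It adds: "The two-sided significance level was 5%, the statistical power was 90%, and the dropout rate was 20"%. The result is 48 patients (24 per group), raised to 62 (31 per group).
- **Rank of the improvement rate.** Outcome measurements closes its list of secondary indicators with a stroke improvement rate, which it does not define.
- **Effectiveness rule.** Data analysis says: "The effectiveness measurement index is the improvement rate of each clinical scale at different follow-up times". It defines this as postoperative minus preoperative score, divided by the preoperative score, times 100%. It then adds: "A score improvement rate > 25% is considered effective". Neither sentence mentions the control group, FMA-UE or secondary status.

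**The concern.** A difference in mean points between arms and a percentage change cut at 25% are different endpoints. The first gives a point the same weight in every patient and needs a control arm. The second divides by each patient's own baseline, dichotomises, and as written needs no control arm.

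Data analysis uses verdict wording for the second, and does so for every scale at every follow-up. A reader of that section alone would judge efficacy by the 25% rule, whereas a reader of Sample size would judge it by the difference in means. The two can disagree, and the protocol's power statement covers only the difference in means. If the wording stays, the trial could be reported as effective on the 25% rule although its only stated hypothesis was not rejected, or the reverse.

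**Working it through.** **1. Reproduce the stated sample size.** Sample size gives these inputs: "the mean FMA before DBS treatment was 21.92 ± 6.30, and the mean FMA after DBS treatment was 35.42 ± 12.23", two-sided 5%, power 90%, dropout 20%, 1:1.

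- Difference: 35.42 − 21.92 = 13.50. With a common SD of 12.23, the standardised difference is 13.50/12.23 = 1.10.
- Two-sample t-test: power is 89.6% at 18 per arm and 91.2% at 19, so 19 per arm are needed.
- Dropout: 19/0.80 = 23.75, so 24 per arm and 48 in total. This matches the plan.
- The cited 7-point gain with SD 6.30 also gives 19, hence 24. Both routes are calculations on means. No responder proportion is used or given anywhere.

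**2. The 25% rule as written has no comparator.** At the planning baseline the cut is 0.25 × 21.92 = 5.48 points. Suppose a patient with this baseline gains 6 points under the rehabilitation that both arms receive: 6/21.92 = 27.4%, which counts as effective. If both arms gained 6 points on average, then u1 − u2 = 0. Conversely, a gain of 5 points is 5/21.92 = 22.8%, which does not count, however clearly the arms differ. The rule and the hypothesis can therefore point in opposite directions.

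**3. Power if the proportion above 25% were compared between arms.** The protocol does not specify this comparison, so the following are assumptions: Fisher's exact test, parallel arms (crossover ignored), no mean change in controls, normal change with SD 12.23 in both arms, baseline 21.92 ± 6.30, scores held to 0–66.

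Responder rates come out at about 74% with stimulation and 33% with sham.

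| Analysable per arm | Difference in points, t-test | Proportion above 25%, Fisher |
|---|---|---|
| 19 (behind the 48) | 91% | 66–68% |
| 25 (31 less 20%: 31 × 0.80 = 24.8) | 97% | 82% |
| 31 (no loss) | 99% | 89% |

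The range at 19 is exact enumeration against simulation.

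**4. Sensitivity to the SD.** Adding a change SD of 12.23 to a baseline SD of 6.30 gives a post-treatment SD of √(6.30² + 12.23²) = 13.8, above the quoted 12.23. Matching 12.23 requires a change SD of √(12.23² − 6.30²) = 10.5. Fisher power is then about 80% at 19 per arm and 92% at 25. If only the control change SD is reduced, to 6.30, it is about 91% at 19 and 98% at 25. At a 7-point difference with SD 12.23 in both arms, power at 19 per arm is about 40% for points and 20–21% for the proportion.

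**The case against.** The strongest answer is that the protocol does rank the two measures. Outcome measurements names FMA-UE change as primary and, in the next sentence, puts an improvement rate among the secondary indicators. The abstract, Study design and the main outcome section agree, and the only hypothesis is the difference in means. A secondary measure need not have 90% power. Data analysis also still provides change from baseline and between-group tests, and its 25% sentence can be read as a label for a patient's response.

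Most of this stands. A reader might infer that the protocol leaves the two definitions unranked, with nothing to decide between them. The documents do not support that: the named primary outcome and the stated hypothesis favour the point difference. A reader might also infer that the trial has only about two-thirds power for its efficacy claim. That is not supported either. No between-arm test of the 25% proportion is specified, 19 per arm is the smallest of the plausible analysable numbers above, and the figure moves with the assumed SDs.

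The wording in Data analysis is not rescued. It does not confine the rate to secondary or per-patient use. The rate named in Outcome measurements is not tied to the formula in Data analysis, and the sections therefore conflict on its rank. This is a positive statement in the published text, not a detail left to an analysis plan.

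**Conclusion.** The point holds in this form: Data analysis states an effectiveness criterion that conflicts with the primary outcome and hypothesis given elsewhere, has no comparator, and has no sample size behind it. The 90% power belongs to the difference in mean points, which reproduces the stated 24 per arm; it does not extend to the 25% rule.

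The numerical gap is illustrative. Under the assumptions shown, a between-arm comparison of the proportion above 25% loses about 23 to 25 percentage points of power at 19 per arm, 15 at 25 and 10 at 31. Responder power at 19 per arm rises to about 80–91% under the other SD assumptions tried. The conflict in wording does not depend on any of these figures. It should be corrected, but it does not call the design or the sample size into question.

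**What to change.** In Data analysis, state that the efficacy conclusion rests on the stimulation-versus-sham difference in FMA-UE points, in line with Study design, Sample size and Outcome measurements. Then present the improvement rate and its 25% cut as secondary descriptive summaries, in line with Outcome measurements, and remove the wording that makes the rate the index of effectiveness and declares a rate above 25% effective.

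The cost is two sentences, with no change to data collection, design or sample size. The improvement rates can still be reported; they only stop carrying an efficacy verdict. The change should be made before unblinding.

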### Secondary outcome

#### Balance ability

Stroke patients suffer from balance dysfunction due to impaired control of the brain’s central nervous system and sensory or motor conduction pathways. The Berg Balance Scale (BBS) is mainly used to evaluate the balance and coordination abilities of participants during intervention and follow-up (48, 49). This scale is suitable for patients with strokes of various severity. Through assessment, it can identify whether patients need help with their movements and prompt the patient’s prognosis. It is mainly used in subacute and chronic strokes to predict and evaluate balance after stroke. It has reliability and validity, sensitivity is good, and it is currently the most commonly used international balance scale for stroke patients. The form includes a total of 14 items, each item includes 5 levels (0 to 4 points), with a total score of 56 points. Higher scores indicate better balance ability (49, 50).

Post-stroke Spasticity will be evaluated using the modified Ashworth Scale (MAS), a widely-used assessment method. It measures resistance during passive joint movements, especially suitable for patients with hemiplegia. Muscle spasticity is graded from 0 to 4, with higher grades indicating increased tone. MAS has proven reliable and valuable in clinical settings for assessing upper limb muscle spasticity. Notably, up to 97% of chronic stroke patients with moderate to severe motor impairments experience spasticity (51–53).

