#### Psychological improvement

Patients with post-stroke hemiplegia may develop post-stroke depression (PSD), which is characterized by persistent depressed mood disorder (mood disorder). The overall incidence rate is as high as 40% to 50%, of which about 15% are severe depression, which may be accompanied by severe suicide or even suicidal behavior. This study used the Hamilton Depression Rating Scale (HAMD) for evaluation (63). This scale is simple to operate, has high reliability and validity, and is widely used in clinical applications. Among them, the HAMD-24 is the most clinically used. Therefore, this study evaluated patients before and after HAMD-24 treatment. A total score of more than 8 points indicates the presence of depressive symptoms in patients, and the higher the score, the more severe the depressive symptoms.

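### The rule that a rate above 25% is effective counts only worsening on HAMD and MAS, and cannot be met on FMA-UE from a baseline of 53 or more

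*Protocol article*

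**What the plan says.** The Data analysis section of the protocol article introduces the index with these words: "The effectiveness measurement index is the improvement rate of each clinical scale at different follow-up times". The formula that follows is "scale score at each postoperative time point − preoperative score) / preoperative score * 100" percent, and the criterion is "A score improvement rate > 25% is considered effective". The section gives no exception, no change of sign for any scale, and no rule for a zero or near-maximal preoperative score.

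The scales are described elsewhere in the article:

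- HAMD-24 (Psychological improvement): "the higher the score, the more severe the depressive symptoms". A total above 8 is taken to indicate depressive symptoms.
- MAS (Balance ability): "Muscle spasticity is graded from 0 to 4, with higher grades indicating increased tone".
- FMA (Motor function intervention effect): the motor part has 100 points, "of which the upper limb motor function score is 66 points, the lower limb motor function score is 34 points", and higher is better.
- Entry (Table 1): an FMA motor score from 50 to 84.

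The primary outcome is the change in FMA-UE. The sample size section tests a difference between group means.

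**The concern.** One unsigned percentage is applied to scales that run in opposite directions. Where higher is worse, a positive rate means deterioration, so the criterion picks out the wrong patients. Where the scale is bounded above, the gain needed grows with the baseline until it no longer fits under the maximum.

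This is the only place in the article that defines when a result counts as effective. Followed literally, it would produce reversed responder rates for depression and spasticity. It would also produce an FMA-UE responder rate in which some eligible patients cannot succeed whatever the treatment does.

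**Working it through.** The 25% threshold is a chosen cut-off without a derivation, so there is no figure of the plan's own to reproduce. The check puts the protocol's scale definitions into its formula, rate = (post − pre)/pre × 100%, with success if the rate exceeds 25%.

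**1. Direction (HAMD, MAS; higher is worse)**

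| Change | Rate | Patient is | Rule says |
|---|---|---|---|
| HAMD 8 → 12 | 4/8 = +50% | worse | effective |
| HAMD 20 → 10 | −10/20 = −50% | better | not effective |
| MAS 2 → 3 | 1/2 = +50% | worse | effective |
| MAS 2 → 1 | −1/2 = −50% | better | not effective |

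Every improvement gives a negative rate, the best possible being −100%, so no improvement can exceed +25%. In the first row the patient moves from 8, which is not above the protocol's own cut for depressive symptoms, to 12, which is, and is counted as a success.

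**2. Zero baseline**

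With pre = 0 the formula divides by zero. Grade 0 is a valid MAS grade. A HAMD of 0 is possible in a patient without depressive symptoms.

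**3. Ceiling (scales where higher is better)**

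Success requires post > 1.25 × pre, and post cannot exceed the maximum M, so pre must be below M/1.25.

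| Scale | M | M/1.25 | Unreachable from |
|---|---|---|---|
| FMA-UE | 66 | 52.8 | 53 |
| BBS | 56 | 44.8 | 45 |
| POMA | 28 | 22.4 | 23 |
| BI | 100 | 80 | 80 |

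For FMA-UE the largest possible rate is 14/52 = 26.9% from a baseline of 52 and 13/53 = 24.5% from 53. For BI, 80 → 100 is exactly 25%, which fails because the inequality is strict.

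**4. Are such FMA-UE baselines eligible?**

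The upper entry limit of 84 exceeds the FMA-UE maximum of 66, so the criterion is read as the 100-point motor total. The lower limb contributes at most 34, so the lowest eligible FMA-UE is 50 − 34 = 16 and the highest is 66. A patient with 53 upper-limb and 20 lower-limb points has a total of 73 and is eligible. If the criterion were instead read as FMA-UE itself, eligible baselines would be 50 to 66, and only 50 to 52 could meet the rule. A zero FMA-UE baseline is not eligible under either reading.

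**5. Against the protocol's cited gain**

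The sample size section cites a mean upper-limb gain of 7 points. A 7-point gain gives 7/27 = 25.9% from a baseline of 27 and 7/28 = 25.0% from 28. It therefore counts as effective only from 27 or below. From 28 to 59, where 7 points still fit under 66, the same gain is labelled not effective.

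**The case against.** The strongest objection is that the rule decides little. The primary outcome is change in FMA-UE, the sample size rests on a difference in means, and the Data analysis section plans between-group tests and covariate-adjusted models for change values. No hypothesis, power calculation or decision is tied to the 25% rule. This stands. A reader might infer that the primary analysis is corrupted, and the documents do not support that.

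The reach of the FMA-UE ceiling is also not shown. The only baseline figure in the article, 21.92 ± 6.30, would put 53 at (53 − 21.92)/6.30 = 4.9 SD above the mean. But that figure comes from the literature. If it is an upper-limb score, a patient at that mean would need 50 − 21.92 = 28.08 of the 34 lower-limb points to be eligible, so it is a poor guide to this trial's patients. The affected share is unknown in both directions.

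A reader might also infer that chance baseline imbalance between the two groups of 31 would shift the responder comparison. In the crossover each patient is due both active and sham periods with the same preoperative denominator, and so faces the same threshold in both. The argument reaches only an unpaired group comparison, and its size cannot be derived from the documents.

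The zero-baseline case is minor. The article itself says that up to 97% of chronic patients with moderate to severe impairment have spasticity, and MAS has no row in Table 2.

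Finally, an analyst might read the word improvement as licence to reverse the sign. That would depart from an explicit formula stated for every scale, so the direction error remains.

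**Conclusion.** The point holds, as a should-fix. On HAMD and MAS the rule as written is wrong without qualification: it can label only worsening as effective and never an improvement, and it is undefined at a baseline of 0. On FMA-UE it cannot be met from 53 upward and gives no credit for a 7-point gain from 28 upward. These FMA-UE results rest on the maximum of 66 and on reading the entry criterion as the 100-point motor total. The number of patients affected is unknown.

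The planned primary comparison of FMA-UE change does not use the rule and is not itself altered.

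It would be tempting to turn the cited 7 points into a replacement responder threshold. The documents do not support this. It is a group mean from the literature, the same section's means imply a different gain (35.42 − 21.92 = 13.50), and 7 points cannot be gained from an FMA-UE of 60 or more (66 − 60 = 6).

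**What to change.** In the Data analysis section:

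- State that efficacy is concluded from the between-group (active versus sham) difference in FMA-UE change in points, and not from the 25% rule.
- If a 25% responder rate is kept, label it descriptive only.
- Reverse the sign for HAMD and MAS, or report both as absolute change with a decrease counted as improvement.
- For each scale, report the number of patients whose baseline makes the rate undefined (0) or the threshold unreachable (for FMA-UE, 53 or more).

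The cost is a few sentences and no new data. The change should be made before unblinding, because redefining what counts as effective afterwards would look post hoc.

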**Figure 2 fig2:**
[figure not shown]
Brief flowchart of the entire study with draw. For patients whose electrode is not implanted in the ideal position in CT review after DBS implantation, the device can be temporarily left off, and the follow-up of clinical trials is excluded, and relevant conventional rehabilitation means can be actively given. The health status of patients can be observed at any time, and regular follow-up can be conducted. When all clinical trials are over, the effect of DBS treatment can be observed. If the effect of DBS treatment is better than that of the traditional control group, the electrode position should be adjusted again and DBS treatment should be performed again.

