#### Adverse events

During the treatment process, a small number of patients may experience symptoms such as accidental injuries, skin rupture and bleeding, muscle soreness, joint pain, and rashes. Any adverse events (AEs) during recovery should be documented in a specific CRF with time of occurrence, severity, relationship to the duration of the intervention, and prognosis. Investigators should take necessary measures to deal with all AEs to ensure the safety of the subjects and follow up with the subjects until their physical condition returns to normal levels. All adverse events (such as pain and falls) occurring during intervention and follow-up will be recorded on a case record form (CRF) through monitoring and self-reporting, and the relevance of the intervention will be assessed. The incidence of an adverse event was defined as the number of patients in whom it occurred divided by the number of all patients. Calculate the number and frequency of adverse events, related adverse events (adverse reactions), adverse events leading to withdrawal, and serious adverse events, and provide detailed records (64, 65).

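### The 5% adverse event cut-off declares safety from a point estimate, with no confidence limit, no distinction by seriousness and no stated scope

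*Protocol article*

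**What the plan says.** The Data analysis section of the protocol article sets out the safety assessment in three steps.

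- Indicator: "Safety observation indicators are all postoperative adverse reactions, including surgery-related adverse reactions, device-related adverse reactions, and stimulation-related adverse reactions".
- Rate: "The incidence of adverse events is defined as the number of patients in which it occurs divided by the number of all patients".
- Verdict: "an adverse event rate of less than 5% is considered safe".

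The Adverse events section defines the rate for a single event: "The incidence of an adverse event was defined as the number of patients in whom it occurred divided by the number of all patients". It expects that "a small number of patients may experience symptoms such as accidental injuries, skin rupture and bleeding, muscle soreness, joint pain, and rashes". It has severity recorded on the case report form and asks for separate counts of "related adverse events (adverse reactions), adverse events leading to withdrawal, and serious adverse events, and provide detailed records". No threshold is attached to any of those separate counts.

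On who is counted, the Study design section has every included patient implanted, and the Data analysis section divides by all patients. The Figure 2 caption says that if the electrode is not ideally placed, "the device can be temporarily left off, and the follow-up of clinical trials is excluded".

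**The concern.** Safety is one of the leading aims given in the Introduction, and the Discussion presents the trial as the first of its kind. A stated verdict of safe is therefore likely to be reported and relied on. A rule that compares an observed proportion with 5% takes no account of how imprecise that proportion is with 62 patients. It can call the treatment safe when the true rate is well above 5%, and can withhold the label when the true rate is below 5%. Because one cut-off covers every severity, the verdict also carries no information about how serious the reactions were. Because its scope is not stated, two analysts could apply it to the same data and reach opposite conclusions.

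**Working it through.** **Is there a figure to reproduce?** The protocol gives no calculation for the 5% rule. Its only sample size calculation concerns the Fugl-Meyer score. A two-sample t-test with a difference of 7 points, SD 6.30, two-sided 5% and 90% power needs 19 per group. Then 19/0.8 = 23.75, rounded up to 24, gives the stated 48 in total, which is raised to 62. Safety does not enter.

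**Inputs.** n = 62 (Sample size section). Pass if x/n < 0.05, where x is the number of patients affected (Data analysis section). The true rates below are assumptions, since the protocol gives none.

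**Step 1: where the rule switches.** 3/62 = 4.8% passes; 4/62 = 6.5% fails. So the rule passes when x ≤ 3.

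**Step 2: what a passing result excludes.** Exact (Clopper-Pearson) limits. For x = 0 the upper limit is 1 − (α/2)^(1/n) two-sided and 1 − α^(1/n) one-sided:

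- two-sided: 1 − 0.025^(1/62) = 5.8%
- one-sided: 1 − 0.05^(1/62) = 4.7%

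| Affected | Observed | Two-sided 95% CI | One-sided 95% upper limit |
|---|---|---|---|
| 0/62 | 0% | 0 to 5.8% | 4.7% |
| 1/62 | 1.6% | 0.04 to 8.7% | 7.4% |
| 2/62 | 3.2% | 0.4 to 11.2% | 9.8% |
| 3/62 | 4.8% | 1.0 to 13.5% | 12.0% |

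No passing result excludes 5% two-sided, and only zero events does so one-sided.

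**Step 3: how often the rule says safe.** P(pass) = Σ (x = 0 to 3) C(62, x) p^x (1 − p)^(62 − x).

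| True rate p | P(pass) |
|---|---|
| 3% | 88% (fails 12%) |
| 5% | 62% |
| 8% | 26% |
| 10% | 12% |
| 12% | 5% |

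At exactly 5% the treatment does not meet the plan's own criterion, yet it passes more often than not.

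**Step 4: could the verdict be kept with a confidence limit?** For a two-sided 95% upper limit below 5%, the trial would need 72 patients with no affected patient, 110 with one, 142 with two or 173 with three.

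**Step 5: does the denominator matter?** If, as an assumption, only 48 patients were evaluable, the rule would pass at 2 or fewer (2/48: 95% CI 0.5% to 14.3%; 13% chance of passing at a true rate of 10%). Applied to one group of 31, it would pass at 1 or fewer (1/31: upper limit 16.7%; 17% chance at 10%). The conclusion does not depend on the denominator.

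**Step 6: scope.** Data analysis takes all adverse reactions together and then speaks of a single rate. The Adverse events section defines incidence event by event. If the rule covers any reaction, four patients with minor related reactions fail it and three with serious ones pass. If it applies per type, each type passes at up to 3/62, so several types could each be called safe while many more than 5% of patients are affected. On both readings the cut-off is the same for serious and minor reactions.

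**The case against.** Several parts of the opposing case stand.

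- **Serious events have their own route.** Severity is recorded, serious events and withdrawals due to events are counted separately, and the Data monitoring section sends serious events to the ethics committee and an independent monitoring committee that can advise stopping. The mixing of severities is therefore in the 5% verdict, not in data collection or oversight.
- **One-sided limits are reasonable for safety.** On that basis 0/62 does exclude 5%, so it would be too absolute to say that 62 patients could never support the claim. At a true rate of 10% the rule withholds the safe label 88% of the time. Its leniency is greatest nearer 5% to 8%.

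A reader might also infer more than the documents support.

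- **That patients with misplaced electrodes are left out of the safety rate.** The Figure 2 caption takes them out of trial follow-up, but it also allows their health to be observed and regular follow-up to continue. Table 2 schedules adverse event recording from surgery onward, and the denominator is all patients. Nothing removes them from numerator or denominator. The texts leave the matter open.
- **That 14 of 62 patients (62 − 48) could lack safety data.** That difference is a recruitment allowance in the efficacy calculation and also covers other losses. It is not a forecast of misplaced leads.
- **That muscle soreness would count against the device in the same pool as a serious event.** This assumes the any-reaction reading and that the soreness is judged related. The document settles neither.
- **That the plan never isolates stimulation.** Stimulation-related reactions are a named category. Tabulation by stimulation state is detail that a statistical analysis plan may hold.

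None of this repairs the verdict itself, which uses neither the severity data nor any measure of precision.

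**Conclusion.** The 5% rule is wrong as written. With 62 patients it turns 3 or fewer affected patients into a declaration of safety, although 3/62 is compatible with true rates from 1.0% to 13.5%. It passes 62% of the time at a true rate of 5%, and at 3% it wrongly fails 12% of the time. It does not distinguish serious from minor reactions and does not state which events it covers. These figures assume 62 evaluable patients, independent outcomes between patients and the illustrative true rates above. Smaller denominators leave the conclusion unchanged. Whether implanted patients with misplaced electrodes are counted is an inconsistency to be reconciled, not a demonstrated exclusion.

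**What to change.** Delete the 5% verdict from the Data analysis section. In its place:

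1. Define the safety population as all implanted patients.
2. Report serious and non-serious event rates, each by surgery-, device- and stimulation-related cause, with exact 95% CIs.
3. Give stimulation-related events by stimulation state (on versus sham).
4. Reconcile the Figure 2 caption with the Data analysis section by stating that implanted patients with misplaced electrodes stay in the safety numerator and denominator.

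The cost is mainly analysis wording, plus consistent adverse event recording for patients whom the Figure 2 caption already allows to be observed. Sample size and treatment do not change. The downside is that the trial loses a simple safe label and reports visibly wider uncertainty.
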